### Primary outcome

The primary outcome was change in step counts, as measured by seven days of pedometry at baseline and 12 months post-randomization. Participants were instructed to wear an unsealed G-Sensor 2025 pedometer during waking hours and to record the total daily steps in a log. Pedometers have been shown to be a cost-effective option for objectively assessing activity by measuring step counts [39]. Daily step counts were recorded on a log sheet, along with duration of other physical activity that a pedometer does not capture, such as swimming or cycling. These other activities were converted via their respective MET values to equivalent step counts [40], and included in the calculation of average daily step counts. To increase the accuracy of activities not captured by pedometer, participants were asked to report the number of laps swum (50 metre pool), and the number of kilometres cycled. Each lap swum was deemed equivalent to 363 steps and each kilometre cycled was deemed equivalent to 878 steps. All ‘other’ activities were coded using previously reported step count values (table two) [41]. Average daily step count comprised the total step count, including ‘other activities’, divided by the number of days with 10 or more hours of wear time. Every pedometer was tested for accuracy before every use, on a calibration machine, and had to measure 100 cycles of simulated steps within plus or minus two cycles. Whilst there is concern over the reactivity of participants to wearing pedometers, i.e. walking more during the time they are wearing the device [42], any reactivity should be the same at baseline and follow up. At recruitment, participants could choose to be sent an SMS each morning reminding them to wear the pedometer.

### Accelerometer sub-study

A sub-sample of participants was asked to wear an accelerometer, in addition to the pedometer. Consenting participants were provided with a three axis GeneActiv accelerometer worn at the wrist, recording at 40 Hz at each time point in addition to other study measures. Accelerometer data will be used to describe sitting time, and time spent at different activity intensities, and to validate self-reported steps and PA.

### Demographic and secondary outcomes

#### Self-reported physical activity

Physical activity frequency and duration were measured using eight items from the Active Australia survey [43]. The survey evaluates four types of physical activity in the last week: walking, moderate physical activity, vigorous physical activity, and vigorous gardening or heavy work [43]. The Active Australia survey has demonstrated reliability and validity and acceptable test-retest reliability [44].

#### Sedentary behavior

Sedentary behavior was measured using five items asking about time spent sitting (hours and minutes) during the last working and non-working day in each of the following domains: (a) while traveling to and from places; (b) while at work; (c) while watching television; (d) while using a computer at home; and (e) at leisure not including watching television (e.g., visiting friends, movies, eating out) [45]. The five item measure has demonstrated reliability and validity for sitting time on weekdays, but is less reliable for weekends and less structured leisure activities [45].

#### Quality of life

Quality of life was assessed using the AQoL 8D 35-item survey, which measures quality of life across eight dimensions: independent living, relationships, mental health, coping, pain, sense, life satisfaction, and self-worth [46]. The AQoL 8D has been shown to have strong validity [47] and good reliability [48].

#### Depression

The Centre for Epidemiologic Studies Depression Scale (CES-D) 20-item scale was used to measure depressive symptoms. It was designed to measure depressive symptoms in the general population, and it has acceptable reliability and validity [49].

#### Potential mediators of physical activity

A three month time reference was provided for all of the potential mediators (based on SCT) of physical activity. For purposes of mediation analysis, “regular physical activity” was defined as “30 minutes or more per day over at least 5 days per week, and adds up to 150 minutes or more per week” which is consistent with national guidelines for Australian adults [38].Goals and intentions – Behavioral goal was measured with one item which asked “How likely is it that you will do ‘regular physical activity’ within the next 3 months?” on a scale from 0-100% [50]. To assess action planning, four items were designed to measure plans made in relation to regular physical activity, with a five point Likert-type scale from 1 ‘Not at all’ to 5 ‘Very much’. These four questions have internal reliability ranging from 0.92 to 0.95 [51].Self-efficacy – Nine items were used to measure confidence to participate in regular physical activity, and were measured on a five point Likert-type scale from 1 ‘Not at all’ to 5 ‘Extremely’ [52]. The items show internal reliability from 0.88 to 0.90 [52].Outcome expectations – Ten items were used to measure outcome expectations, on a five point Likert scale from 1 ‘ Strongly disagree’ to 5 ‘Strongly agree’. Five measured positive outcome expectations and five measured negative outcome expectations [52]. With Cronbach alphas of 0.79 for the positive scale, and 0.71 for the negative scale, these measures have adequate validity and reliability for use in a general adult population [52].Social support – Two items were used to measure social support in relation to participating in regular physical activity on a five point Likert-type scale from 1 ‘Not at all’ to 5 ‘Very much’ [50] with a correlation of 0.57 in the total sample [53].Perceived environmental local surroundings – Nine items were used to assess the local suburb’s physical surroundings (1. Greenery; 2. Interesting things to look at; 3. Pleasant natural features; 4. Footpaths on most streets; 5. Footpaths that are well-lit at night; 6. Lots of traffic; 7. Live near busy road; 8. Unsecured dogs; 9. Feel safe walking home at night) [54]. The reliability of these nine items has been reported as moderate to substantial, with individual item ICCs ranging from 0.51 to 0.74 [54].

### Socio-demographic and medical characteristics

Thirty questions were used to assess socio-demographic and medical characteristics (date of birth, country of birth, gender, marital status, level of education, income, work status), waist circumference (self-measured using a provided paper tape measure and standardized instructions), weight, height, health status and lifestyle behaviors, dog ownership and time spent walking with the dog, and participant preferences for study group allocation. Where possible, survey items were taken directly from, or based on, validated surveys [55-58].

### Contamination and adverse events

At three month and 12 month follow-up surveys, participants were asked to report on their use of any physical activity health education or promotion programs, the factors that influenced their physical activity levels since the previous survey, and recall any falls or injuries since the previous survey. The checklist completed by EPs after each consultation also prompted recording of any falls or injuries suffered by the participant.

### Follow-up and minimization of attrition

Since attrition reduces the effective sample size and can introduce bias, strategies shown to increase response to questionnaires in a Cochrane review were employed [59]. Accordingly, if the completed survey, pedometer and pedometer log sheet was not received after two weeks, participants received a reminder postcard. If not received after a further two weeks, participants received a reminder telephone call or reminder email, and a second copy of the questionnaire was mailed, if requested. Participant attrition and adverse events were monitored at each stage of the trial by the Research Manager.

### Sample size

A sample size of 79 participants per group will provide 90% power to detect a differential increase of 1000 steps per day at 12 months between the two intervention groups and the usual care group at the 5% significance level. This sample size was calculated assuming that the usual care group will increase their average daily step count by 1000 steps, and the standard deviation of 2500 observed in the pilot study. Attrition rates are estimated to be 10% over the twelve month period [60]. This results in a total required sample of 261 (n = 87 per group).

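### The stated 90% power with 79 per group does not follow from the stated inputs on their ordinary reading, which give about 82% for the pooled primary comparison

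*Protocol article*

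**What the plan says.** The protocol article, Sample size, states: "A sample size of 79 participants per group will provide 90% power to detect a differential increase of 1000 steps per day". The contrast is described as "between the two intervention groups and the usual care group at the 5% significance level". Two assumptions are given: usual care itself rises by 1000 steps ("assuming that the usual care group will increase their average daily step count by 1000 steps"), and variability is "the standard deviation of 2500 observed in the pilot study". After 10% attrition, "This results in a total required sample of 261 (n = 87 per group").

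Three other sections fix what is being powered. Primary outcome defines the endpoint as change in step count from baseline to 12 months. Randomization and blinding allocates 1:2 to usual care and intervention, then splits the intervention group 1:1. Statistical analyses makes the combined intervention groups against usual care the primary comparison, in a linear mixed model that constrains the baseline means to be equal.

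The article does not say whether the test is one- or two-sided, whether 2500 is the SD of a single-visit step count, of change, or of a baseline-adjusted value, or what correlation between visits was assumed.

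**The concern.** A reader who puts the published difference, SD, significance level and group sizes into the usual two-mean formula does not get 90%. A 5% level with no qualifier is normally read as two-sided. An SD quoted beside a difference in change, for an endpoint that is change, is normally read as the SD of that change. On that reading the power is about 82%.

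The primary test matters beyond its own result. Under Statistical analyses, face-to-face and telephone counseling are compared only if the primary analysis is significant. The Abstract and Discussion make the equivalence and cost-effectiveness assessment conditional on efficacy. If power is below the stated figure, the trial is less likely to reach those later questions than a reader would expect.

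**Working it through.** **Inputs.** From Sample size: difference d = 1000 steps/day, SD s = 2500, 5% level, 79 completers per group, 10% attrition, 87 enrolled per group. From Randomization and blinding and Statistical analyses: pooled intervention against usual care, so 158 v 79. The 1000-step rise in usual care drops out once the differential is fixed.

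**Formulas.** SE = s × √(1/158 + 1/79). Power ≈ Φ(d/SE − z), with z = 1.960 (two-sided 5%) or 1.645 (one-sided 5%). Usual-care n for 90% power at 2:1 = 1.5 × [(s/d) × (z + 1.282)]². Noncentral t results are given alongside.

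**Trying to reproduce 90% at 79**

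1. *Two-sided, 2500 as the SD of the analysed change.* SE = 2500 × √(1/158 + 1/79) = 344.5, and d/SE = 2.90. Power = 82.7% (normal), 82.4% (t). The n for 90% is 1.5 × (2.5 × 3.242)² = 98.5, so 99 per group (100 by t). The difference detectable with 90% power at 79 per group is 344.5 × 3.242 = 1117 steps (1121 by t), or about 1120.

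2. *One-sided 5%, same SD.* Power = 89.6% (normal), 89.4% (t). The n for 90% is 1.5 × (2.5 × 2.927)² = 80.3, so 81 per group. This is close to the stated figures but not exact.

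3. *Two-sided, 2500 as a single-visit SD.* For 90% at 79 per group the effective SD must be 1000 / (√(1.5/79) × 3.242) ≈ 2239.
 - With baseline adjustment, effective SD = 2500 × √(1 − r²). It equals 2239 at r ≈ 0.445.
 - With a raw change score, effective SD = 2500 × √(2(1 − r)). At r = 0.6 this is 2236, which gives n of about 79.

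The article gives no r, so the values below are assumptions. Two-sided power, 158 v 79, normal approximation:

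| Assumed r | Baseline-adjusted | Change score |
|---|---|---|
| 0.3 | 86.1% | 68.9% |
| 0.4 | 88.6% | 75.5% |
| 0.5 | 91.8% | 82.7% |
| 0.6 | 95.2% | 90.1% |

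The constrained model in Statistical analyses has roughly the precision of baseline adjustment, so that column is the relevant one if 2500 is a single-visit SD.

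**Attrition.** 79 × 1.1 = 86.9, which matches the stated 87. Losing 10% of 87 leaves 87 × 0.9 = 78.3. Keeping 79 needs 79/0.9 = 87.8, so 88. With 156 v 78, the two-sided power in step 1 is 81.9% instead of 82.4%, a change of half a point.

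**The case against.** The strongest reply is that the section fixes neither the sidedness nor the meaning of 2500, so 82% is the result of one reading only. A one-sided 5% test of the protocol's own primary contrast comes within about half a point of 90%. If 2500 is a single-visit SD, the planned model reaches 90% at a correlation of about 0.45 and exceeds it above that. An article also condenses a fuller protocol, where these details may be given.

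Much of this stands. A reader might infer that the trial is in fact underpowered, with an 18% chance of missing a 1000-step effect. The article does not establish that: under baseline adjustment with a single-visit SD, power could be anywhere from about 86% to 95% over assumed correlations of 0.3 to 0.6. A reader might also compare one intervention arm with usual care (79 v 79) and infer a larger shortfall. No power is claimed for that contrast and it is not primary, so it says nothing against the 90%. A change-score sensitivity range taken alone would also mislead, because the planned analysis is not a raw change score.

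The reply does not remove the mismatch. The article chose to publish a power figure together with its inputs, and each route to 90% at 79 per group needs something it does not declare. A one-sided primary test would be a consequential choice that readers should be told about. The point is therefore that the printed inputs do not yield the printed figure, rather than that a detail has been left out.

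**Conclusion.** The point holds in this form: with a two-sided 5% test and 2500 as the SD of the analysed change, 79 completers per group give about 82% power for the pooled primary comparison, not 90%, and 90% would need about 100 per group. The reading rests on two conventions that the article does not contradict: an unqualified 5% level is two-sided, and the SD quoted for a change endpoint is the SD of change. If either is wrong, 90% may be roughly right or even conservative, but the text would then have to say so. The attrition slip is minor, at one participant per group and about half a percentage point of power.

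**What to change.** Reword the Sample size paragraph, leaving enrolment as it is.

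- If the test is two-sided and 2500 is the SD of change, state that 79 completers per group (158 v 79) give about 82% power for 1000 steps, or 90% power for about 1120 steps.
- Otherwise, state the sidedness, what 2500 is the SD of and the baseline to 12-month correlation used, and give the power on that basis under the constrained model. Power should not be restated as 82% until the meaning of 2500 has been checked against the pilot data.
- In either case, say that 87 per group with 10% attrition leaves about 78 completers, or give 88 per group as the number that keeps 79.

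The cost is one paragraph of text. In the first case the stated power also becomes less favourable.

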### Randomization and blinding

Random allocation of eligible participants was conducted in two stages, and in order to offer participants a service that was geographically accessible they were asked to indicate the suburbs where they would prefer to see an EP. First, eligible patients were randomly assigned in a 1:2 ratio to the usual care group or to the intervention group using a randomized block design stratified by participant gender with block sizes of 6. Second, those allocated to the intervention group were randomly assigned in a 1:1 ratio to face-to-face only or face-to-face and telephone counseling using a randomized block design stratified by participant gender and the suburb location of the EP, using block sizes of 6. The randomization process occurred on computer at a centralized location by an independent statistician. Participants were notified of group allocation by letter. Central randomization allowed concealment of allocation from research assistants and GPs until group assignment had occurred. Blinding of participants and EPs was not feasible. Contamination was minimized as the intervention was not delivered at the primary care site and follow-up data collection occurred by mail, with patient-reported survey and pedometer-assessed step counts, so was not influenced by study team members. The data analyst was blinded to group allocation, as surveys were de-identified and did not contain study group information.

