#### Group 2: referral for face-to-face and telephone physical activity counseling

Participants randomized to Group 2 attended one face-to-face consultation (60 minutes) with an EP and participated in four telephone counseling sessions with the same EP over the 13-week intervention period. The telephone calls were expected to take 30 minutes. The aims and content of the initial and subsequent consultations were the same as for Group 1.

If an EP assessed during the initial face-to-face consultation that the patient in either Group 1 or Group 2 had a complex medical issue that would prevent them from being able to safely undertake increased exercise without appropriate supervision, then participants were deemed ineligible, and were excluded from the intervention and follow-ups.

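### The 10% attrition allowance multiplies by 1.10 instead of dividing by 0.90, so 87 per group leaves about 78 with 12-month data, just under the 79 required

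*Protocol article*

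**What the plan says.** The Sample size section of the protocol article builds the target in three steps.

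- The base requirement: "A sample size of 79 participants per group will provide 90% power" for a difference of 1000 steps per day at 12 months, "at the 5% significance level", using "the standard deviation of 2500 observed in the pilot study".
- The expected loss: "Attrition rates are estimated to be 10% over the twelve month period".
- The result: "This results in a total required sample of 261 (n = 87 per group").

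The section does not say how the 10% was applied. Three equal groups follow from the Randomization and blinding section, where "eligible patients were randomly assigned in a 1:2 ratio to the usual care group or to the intervention group" and the intervention group is then split 1:1.

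**The concern.** The 79 per group is the number to which the power statement is attached, and the step to 87 is there to protect it against loss by 12 months. An attrition rate is a fraction of those who start, so the number to randomize is the required number divided by the fraction retained. The stated 87 looks like the required number increased by 10%, which always falls a little short. If so, the target called required does not deliver the number the same section says is needed, at the loss rate the same section expects. What is at stake is the accuracy of a stated sample size and a small amount of power. The design and the analysis are not affected.

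**Working it through.** **Inputs**, from the Sample size section unless noted:

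- required per group n = 79
- attrition d = 0.10
- groups = 3
- stated result: 87 per group, 261 in total
- for the effect on power: difference 1000, SD 2500, 5% level. The two intervention groups are pooled against usual care (2:1), as in the primary comparison of the Statistical analyses section. Sidedness is not stated, so both versions are shown.

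**1. Reproducing the stated figure**

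n × (1 + d) = 79 × 1.10 = 86.9, rounded up to 87; 87 × 3 = 261. This matches exactly.

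**2. Allowing for a 10% loss from those randomized**

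n / (1 − d) = 79 / 0.90 = 87.8, rounded up to 88; 88 × 3 = 264. Check: 88 × 0.90 = 79.2, which meets 79.

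**3. Running the stated figure forward**

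- Per group: 87 × 0.90 = 78.3, against 79; shortfall 0.7.
- In total: 261 × 0.90 = 234.9, against 79 × 3 = 237; shortfall 2.1.

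**4. The loss that 87 can absorb**

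1 − 79/87 = 8/87 = 9.2%.

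**5. Effect on power**

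Normal approximation, with n in usual care and 2n in the pooled intervention groups: power = Φ(1000 / [2500 × √(1/n + 1/(2n))] − z), where z = 1.960 two-sided or 1.645 one-sided.

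| n in usual care | two-sided 5% | one-sided 5% |
|---|---|---|
| 79 | 82.7% | 89.6% |
| 78.3 | 82.4% | 89.3% |

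The unrounded differences are 0.3 points two-sided and 0.2 points one-sided. The absolute levels in this table depend on the sidedness and variance assumed. Only the differences between its rows bear on this point.

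**The case against.** The best defence is that the discrepancy is at the level of rounding. The 10% is described as an estimate, and the gap between 10% and 9.2% is well within the uncertainty of any such forecast. The primary analysis is also a mixed model over baseline, 3 and 12 months, so someone lost after 3 months still contributes data, and 78 against 79 completers is not a sharp threshold. All of this stands, and it is why the point is minor. It does not make the figure right: the section sets its own requirement and its own loss rate, and 87 misses the first at the second. Rounding does not rescue it either, because 87.8 does not become 87 by ordinary rounding or by rounding up.

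Two stronger readings are tempting, and the document supports neither.

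- A reader might infer that 261 cannot be obtained from the trial's own figures. It can: 79 × 1.10, rounded up and multiplied by 3, gives it exactly. The fault lies in the method of inflation; the source of the number is clear.
- A reader might infer a second, unallowed loss in the intervention arms, because patients whom the exercise physiologist finds unable to exercise safely without supervision "participants were deemed ineligible, and were excluded from the intervention and follow-ups" (section on Group 2, applying to Groups 1 and 2). The Sample size section neither defines attrition nor leaves these patients out of it. No rate is given, and silence on replacement in a condensed article is not a rule against it. Screening before randomization should also keep such removals down. Since the primary comparison pools Groups 1 and 2, a shortfall counted arm by arm would overstate the effect. This cannot be added to the arithmetic point.

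**Conclusion.** The point holds as a small arithmetic slip. The allowance was evidently made by multiplication; division gives 88 per group and 264 in total, one more per group and three more overall (3/261 = 1.1%). At the stated 10% loss, 87 per group is expected to leave about 78 per group, 235 in total, with 12-month data. The cost is about 0.2 to 0.3 points of power.

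The completer counts rest only on the figures in the Sample size section and on reading attrition as a fraction of those randomized. The power differences further assume a normal approximation, SD 2500 and 2:1 pooling. That the authors multiplied is inferred from the exact match, since the article does not state the method.

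Nothing here checks or endorses the claim that 79 per group gives 90% power. That depends on sidedness and on any variance reduction assumed, and needs to be examined separately.

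**What to change.** Correct the sentence that gives the total, in one of two ways: 87 per group (261 in total) allows for about 9% loss by 12 months; or 87 per group with 10% loss leaves about 78 per group with 12-month data. Do not present 261 as securing 79 per group at 10% attrition.

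This is a change of wording only. It needs no added recruitment and no change to design or analysis. The one cost is that the stated figure becomes slightly less favourable.
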